### Plans to give access to the full protocol, participant-level data and statistical code {31c}

After finalising the project, access restrictions will be applied to the pseudonymised data and will be specified in a data use agreement containing the following elements: evaluation of the re-use request by ethical committee, non-disclosure agreement and warranties for safe storage of data.

## Oversight and monitoring

### Composition of the coordinating centre and trial steering committee {5d}

The Steering Board is the main decision-making and steering body of the project. The Steering Board consists of [name], [name], [name], [name], [name] and [name] The extended Steering Board consists of the Steering Board, together with the project coordinator and three predoctoral students. The Steering Board organised a kick-off meeting at the start of the project to establish common working procedures. All Steering Board members are responsible for the internal communication within their own institution. The main tasks of the Steering Board are (1) agree on common working procedures and management policies, (2) monitor overall progress and follow-up of deliverables, (3) decisions on major changes to the work programme, (4) conflict handling and (5) budget decisions. One of the most important tasks of the Steering Board is also to (re)direct all participants in the implementation of the work programme and the timely achievement of all deliverables. The Extended Steering Board will further assemble meetings at least every 6 months. Additional teleconferences can be organised ad hoc in case of urgent issues. The Extended Steering Board is responsible for assuring the quality of the workflow and project implementation, considering the available resources. The principal investigators in the recruiting centres are responsible for patient recruitment and form the OPERA consortium, together with the Extended Steering Board.

The valorisation board consists of relevant stakeholders (*N*=7) who will be asked to actively contribute to the implementation of the study findings, and any difficulties experienced during the implementation process will be discussed. The researchers are available to support the stakeholders with the implementation process. In addition, the valorisation board will prepare and guide the full utilisation process in the period following the completion of the research project (after-trajectory), together with the Extended Steering Board.

### Composition of the data monitoring committee, its role and reporting structure {21a}

The study coordinator at Vrije Universiteit Brussel will regularly monitor data that are entered in Qualtrics and in the Excel file for the functional capacity evaluation. The study coordinator is independent from the funder of this study and has no competing interests.

### Adverse event reporting and harms {22}

All adverse events (AEs) reported spontaneously by the patient or observed by the assessor will be recorded. Serious adverse events (SAEs) will be reported to the (local) principal investigators as soon as possible, who will be responsible for informing the ethics committee. Reporting suspected unexpected serious adverse reactions (SUSARs) is not applicable, since this study does not include a medicinal product.

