In patients with chronic low back pain without previous spinal surgery, multidisciplinary biopsychosocial rehabilitation programmes proved to be beneficial to promote work resumption [12, 13]. For patients with persisting or recurring pain after previous spinal surgery, who started with SCS as a pain management strategy, descriptions of rehabilitation programmes and concrete paramedical therapy guidelines to improve RTW are scarce. Physical therapy guidelines after SCS implantation promote a patient-centred approach to address individual needs, values and goals with special attention for the risks of lead migration or fracture and/or damage to SCS componentry [14]. The lack of high-intensive RTW rehabilitation in this group presumably leads to the low percentage of patients that returns to their previous professional activities. Therefore, we propose a personalised biopsychosocial rehabilitation programme to improve RTW for patients with PSPS-T2, implanted with SCS.

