### Intervention description {11a}

#### Experimental intervention: a personalised biopsychosocial RTW programme

The experimental intervention consists of a personalised biopsychosocial RTW programme, which will be provided at each centre. This 14-week programme will start 6 weeks (±1week) after implantable pulse generator (IPG) implantation and comprises 30 treatment sessions, delivered by trained physiotherapists, occupational therapists and psychologists. All therapists will be rigorously trained by experts in the different therapy modalities through a training session (half day) consisting of general project information as well as a specific training for the intervention that the therapist will deliver (i.e. physiotherapy, occupational therapy or pain neuroscience/RTW education). Each therapist will receive a written handbook with a detailed description of the content of each interventional session, as well as a checklist of topics that have to be covered per session and accompanying slides per session (except for physiotherapy sessions no slides are foreseen since the sessions only consist of exercises). Refreshment courses will be foreseen for all therapists (at least on an annual basis). Patients receive a written booklet with the content of the pain neuroscience education, a summary of the occupational sessions and home exercises for physiotherapy.

The programme starts with educational sessions regarding pain neuroscience and the key attributes of a RTW programme and nutritional advice. This will be followed by a session to determine individual treatment goals. The IMBA methodology (Integration von Menschen mit Behinderungen in die Arbeitswelt) [21] will be used to compare work requirements and work ability, while a functional capacity evaluation will be used to select relevant treatment sub-goals for the physical therapy and occupational therapy with the aim of being physically capable to work. As such, a standardised treatment plan, based on the type of job and the functional capacity of each patient, will be constructed with specific goals for both the physiotherapist and occupational therapist. To monitor treatment progress and enable adjustments to the rehabilitation plan, a shortened version of the functional capacity evaluation will be assessed at the beginning of week 8. Table 1 presents an overview of the content of the experimental intervention.

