#### Control intervention: usual care

Patients randomly allocated to the control intervention will undergo the usual care trajectory. This programme is delivered at each of the participating centres. Patients will follow the usual care as it is implemented in Belgian hospitals, after SCS implantation. After implantation, patients are seen by the treating physician, pain nurse(s) and/or delegates of the companies of the SCS devices to programme the SCS parameters. On top of that, they have a fixed 6-month follow-up appointment to re-evaluate the therapy and evaluate medication use in combination with SCS. Each hospital can continue the usual care as normally provided to patients after SCS implantation. The normal trajectory of re-integrating patients will be followed and recorded.

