### Provisions for post-trial care {30}

This study does not provide post-trial care. There is no anticipated harm for trial participation and consequently no compensation for anticipated harm.

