## Assignment of interventions: blinding

### Who will be blinded {17a}

The statistician, outcome assessors and treating physicians (neurosurgeons or anaesthesiologists) will be blinded to group allocation. With regard to this, patients will be asked not to communicate with the assessors about the intervention received. Furthermore, at the end of each assessment, the success of assessor blinding will be examined by asking whether the assessor thought the patient had received the experimental or control intervention, including the percentage of certainty (i.e. 50% certainty means a pure guess).

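### Adverse events are captured only passively, so recording may be incomplete in both arms and may differ between them in an unsettled direction

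*Protocol article*

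**What the plan says.** All references are to the protocol article.

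- **Capture rule**, Adverse event reporting and harms {22}: "All adverse events (AEs) reported spontaneously by the patient or observed by the assessor will be recorded". For serious events, "Serious adverse events (SAEs) will be reported to the (local) principal investigators as soon as possible". The section describes no routine enquiry and no predefined device events, and does not mention therapists.
- **Contact by arm**, Intervention description {11a}: the 14-week programme "comprises 30 treatment sessions, delivered by trained physiotherapists, occupational therapists and psychologists". For controls, "Each hospital can continue the usual care as normally provided to patients after SCS implantation". Usual care includes contacts to programme the stimulator and a set review at 6 months.
- **Blinding**, Who will be blinded {17a}: assessors are blinded, and "patients will be asked not to communicate with the assessors about the intervention received".
- **Assessments**, Outcomes {12} and Plans for assessment and collection of outcomes {18a}: six assessments on one schedule, not distinguished by arm. Five of them fall after implantation.
- **Foreseeable device risk**, Background and rationale {6a}: guidelines for physical therapy after implantation call for "special attention for the risks of lead migration or fracture and/or damage to SCS componentry".
- **Expected harm**, Provisions for post-trial care {30}: "There is no anticipated harm for trial participation and consequently no compensation for anticipated harm".
- **Related data**, Healthcare expenditure: weekly diaries during the intervention and questionnaires at the other visits cover admissions, treatments and consultations.
- **Use of the result**, Discussion: if more effective than usual care, the programme should become standard for these patients.

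**The concern.** A spontaneous report needs someone to receive it, and the two arms differ in how often a patient meets study-related staff. The only observer the harms section names is the assessor, who is blinded and to whom patients are asked not to speak about their intervention. A problem that arose in an exercise session is hard to mention without breaking that request.

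The programme includes strength, stabilisation, dynamic and lifting-related training in patients with implanted leads. Hardware problems are therefore the harms a reader would most want counted evenly. If the trial favours the programme and its adoption is recommended, the recorded events will be the available evidence on that risk. Events not asked about during follow-up cannot be reliably reconstructed afterwards.

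**Working it through.** The protocol states no figure on this point, so there is none to reproduce. The check is a reading of the sections side by side, followed by an illustration with assumed values.

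**1. Who can record an event.** Section {22} gives two routes: the patient volunteers it, or the assessor sees it. It does not say to whom the patient volunteers it.

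**2. Contact.** Assessor contact follows the same schedule in both arms. The designed difference is the 30 therapist sessions. A ratio of total contacts cannot be formed fairly: usual-care contacts are not counted in the document, and some programme sessions are held in groups or online.

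**3. Two readings of the rule.**
- If remarks to therapists are recorded, programme patients have more occasions to report, and capture is probably higher in that arm.
- If they are not recorded, the sessions add little to capture. The request not to discuss the intervention may then suppress therapy-linked reports, so capture could be lower in the programme arm.

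The document does not choose between these readings.

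**4. Effect on a recorded ratio.** Let p be the true risk and c the probability that an event is recorded, with E the programme arm and C the control arm:

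recorded ratio = (p_E × c_E) / (p_C × c_C)

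If the true risks are equal, this reduces to c_E / c_C. All values of c below are assumptions.

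| c_C | c_E | Recorded ratio, equal true risk | Recorded ratio, true doubling in programme arm |
|---|---|---|---|
| 0.5 | 0.5 | 1.0 | 2.0 |
| 0.5 | 0.7 | 1.4 | 2.8 |
| 0.5 | 0.9 | 1.8 | 3.6 |
| 0.3 | 0.9 | 3.0 | 6.0 |
| 0.7 | 0.5 | 0.71 | 1.43 |
| 0.9 | 0.5 | 0.56 | 1.11 |

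The first row shows that equal under-capture loses events without distorting the ratio. The other rows show that unequal capture can create a difference or hide one.

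**5. Can the trial detect a doubling of device events?** Assume true risks of 10% and 20%, and a two-sided test at 0.05. Power by exact enumeration:

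| Per arm | Capture | Recorded risks | Fisher exact | Chi-square |
|---|---|---|---|---|
| 56 | all | 10% vs 20% | 22.5% | 32% |
| 56 | half | 5% vs 10% | 8% | 16% |
| 50 | all | 10% vs 20% | 19.5% | 30% |
| 50 | half | 5% vs 10% | 6% | 14.5% |

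The figure of 56 per arm is from Sample size {14}. The figure of 50 applies that section's 11.3% trial-failure allowance: 112 × 0.887 = 99.3, or about 50 per arm if failures are evenly split. Power is low with full capture as well, so better capture improves the description of harms but does not support a formal test.

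**The case against.** The strongest case on the other side has five parts.

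- **No harm comparison is promised.** Harms are not among the objectives or listed outcomes. This stands: there is no planned between-arm analysis to call invalid. The point concerns the quality of data that will be relied on if adoption is recommended.
- **The named observer is even-handed.** Assessors are blinded and follow one schedule, and controls also have clinical contacts at which a device fault could be raised. This stands as a limit on the asymmetry. A reader might infer that the programme arm will show inflated event counts, but the document does not support that, because it does not say whether therapist-reported events are recorded. The bias could run either way.
- **Another source exists.** Healthcare-use diaries and questionnaires may reveal device problems that led to care. This stands in part. They are collected as cost data, record use of care rather than events, and are not linked to adverse-event recording.
- **The article is condensed.** Forms and therapist instructions may sit in documents not shown, such as the therapists' handbook. This is fair as to detail. However, the article does state its capture rule, and that rule is passive.
- **The wording conflict is narrow.** A reader might see a flat contradiction over harm. In fact the Background summarises guidelines for stimulator patients generally, while section {30} concerns post-trial care and compensation. The two statements sit badly together, but the remedy is a wording edit.

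**Conclusion.** The concern holds in a limited form. The stated rule is passive, and contact differs by design. Patients have also been asked not to discuss their intervention with the only named observer. Incomplete recording in both arms is likely, and unequal recording is possible. Neither its size nor its direction can be obtained from the document. The ratios of 0.56 to 3.0 under equal true risk rest entirely on assumed capture probabilities and only show what unequal capture can do.

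A reader might also infer that passive capture is what prevents the trial from detecting a doubling of device events. It is not: at an assumed 10% control risk, power is at most about 32% even if every event is recorded.

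The point does not touch the primary outcome or its analysis. It should be acted on because an even-handed method is cheap and the proposed use of the result calls for credible data on the hardware risks the protocol itself names.

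**What to change.** 1. At each of the five existing assessments after implantation, ask both arms the same open adverse-event question and a short fixed list of stimulator hardware events (lead migration, lead fracture, device damage, revision). The 6-week assessment precedes the programme, so it also separates earlier events from later ones. Word the items so that an answer need not reveal the allocation.
2. Summarise these solicited events by arm descriptively, without a formal test.
3. State whether therapists record events, and list separately those that came to light only through therapy sessions.
4. Reconcile the sentence "There is no anticipated harm for trial participation" in section {30} with the hardware risks named in the Background.

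The cost is a few minutes per visit, one extra form and more minor events to record. No new visits or staff are needed, and neither the treatment nor the primary analysis changes. For patients already in follow-up, the questions can start at their next assessment, and the summary should show the date from which solicited capture began.

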### Frequency and plans for auditing trial conduct {23}

The study staff will submit a summary of the progress of the trial to the central ethics committee once a year. Information will be provided on the date of inclusion of the first subject, numbers of subjects included, numbers of subjects that have completed the trial, serious adverse events/serious adverse reactions, other problems and amendments. There is no planned on-site auditing of the trial. However, to ensure compliance with relevant regulations, an independent quality assurance representative may review this study. This implies that auditors will have the right to audit the site(s) at any time during and/or after the completion of the study and will have access to the data generated during the clinical investigation, source documents and patient’s files.

### Plans for communicating important protocol amendments to relevant parties (e.g. trial participants, ethical committees) {25}

All protocol amendments will be approved by the ethics committee prior to implementation. If relevant, patients will be informed of protocol modifications.

### Dissemination plans {31a}

Given the high value of the results for patients, clinicians, society and other stakeholders, the implementation of this rehabilitation programme in clinical settings is the primary goal. All stakeholders will be contacted during the execution of the project to start introducing this rehabilitation programme in relation to PSPS-T2 patients. Regular updates will be provided to all stakeholders to keep everyone informed, involved and motivated for this project. Furthermore, we will communicate findings of this project via the publication of scientific manuscripts and presentations on national and international symposia, as well as through social media. Furthermore, we will write a summary of the main study findings in layman’s terms for patients’ organisations and charities. Additionally, social instances will be contacted, and presentations will be given to make them aware of the study findings.

## Discussion

The OPERA study will evaluate whether a multidisciplinary biopsychosocial approach for improving RTW is different from usual care in terms of work ability for patients with PSPS-T2 after SCS implantation. This allows us to tackle the high burden of patients that are not re-entering the labour market by proceeding towards a personalised multidisciplinary evidence-based conservative intervention for a costly and debilitating condition. If the new intervention, consisting of a personalised biopsychosocial RTW rehabilitation programme, is more effective than the usual care alone for improving work ability in PSPS-T2 patients after SCS implantation, then the new therapy should be applied as the new standard conservative treatment for these patients. Therefore, this project holds the potential to have utilisation goals for several stakeholders among which patients themselves to improve their work ability, health professionals since new treatment guidelines could be developed based on the results of this project and the health security system since the study findings may allow for scientifically evidence-based decision-making, in order to decrease expenses of the public and private health security systems accompanied by PSPS-T2 patients with SCS that are not resuming work.

Furthermore, these study findings could open avenues for similar studies evaluating the benefits of this multidisciplinary programme in patients after failed surgery, where RTW is currently not achieved (i.e. interdisciplinary rehabilitation programme after surgery as such). Hence, the project has the potential to significantly impact upon the progress of science and clinical practice in the field of “failed surgery” (i.e. applicability for other patient groups in whom RTW is not achieved). The awareness is growing that the burden of PSPS-T2 on our society is expected to increase over time due to the annual increase of spinal surgeries [72], but innovative and methodologically rigorous trials exploring the potential to decrease the socio-economic burden are essentially lacking.

### Trial status

Recruitment has started in April 2022 and will be ongoing until 112 patients are included in the study (expected end date December 2023). The current protocol is version 3 of May 2022.

## Data Availability

The Extended Steering Board has access to the pseudonymised final trial dataset. Any materials to support the protocol can be supplied on motivated request, under the condition that the current study is not compromised.

## Abbreviations

EQ5D-5L: EuroQol with five dimensions and 5 levels
FCE: Functional capacity evaluation
HADS: Hospital Anxiety and Depression Scale
HE: Healthcare expenditure
IMBA: Integration von Menschen mit Behinderungen in die Arbeitswelt
ODI: Oswestry disability index
PSPS-T2: Persistent spinal pain syndrome type II
OR: Odds ratio
PAM: Patient activation measure-13
PSQI: Pittsburgh Sleep Quality Index
RTW: Return to work
SCS: Spinal cord stimulation
TSK: Tampa Scale for Kinesiophobia
VAS: Visual analogue scale
WAI: Work Ability Index
WORQ: Work Rehabilitation Questionnaire
